#### Exclusion criteria

The exclusion criteria will be as follows: (1) severe physical or psychological symptoms (cognitive dysfunction [defined as a score of ≤ 23 on the MMSE-J performed for all prospective participants aged ≥ 65 years or those aged 20–64 years who did not seem to understand routine instructions during the preliminary interview], impaired consciousness, severe depression with psychotic symptoms, imminent suicidal ideation, and history of suicide attempt); (2) receipt of psychological intervention, such as BA, by mental health professionals before enrollment; (3) use or planned use of any psychotropic drug during the program, except for temporary emergency use after enrollment based on the discretion of the attending physician; (4) substance dependence based on the diagnostic criteria in the Diagnostic and Statistical Manual of Mental Disorders, 5th edition; and (5) difficulty in participating in this program due to other reasons, according to the attending physician or researchers.

The waiting group will be informed that if the need for medication arises during the waiting period, they will be excluded from the study but can be offered another program equivalent to the BA program if they wish.

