#### Discontinuation criteria

The discontinuation criteria will be as follows: (1) serious adverse events or adverse reactions that make it difficult to continue the intervention; (2) worsening of physical or psychiatric symptoms, or emergence of new symptoms that make it impossible to continue the intervention; (3) patient desire to discontinue the intervention; (4) interval of 1 month or more between sessions attended; (5) regular use of psychotropic drugs at the discretion of the attending physician during the implementation of the program or while waiting; (6) meeting the exclusion criteria while waiting; and (7) any other reason for which the attending physician deems it necessary to discontinue the intervention.

If this study will be discontinued, the date on which the decision for discontinuation was made and the reason for discontinuation will be noted on the case registration form. The data center will be informed of the discontinuation.

If serious adverse events or adverse reactions, such as worsening of psychiatric or physical symptoms, occurs and it is deemed difficult to continue the intervention, the therapist will promptly inform the research director at each research institution and discontinue this study. The research director at each research institution contacted will promptly inform the research representative and data center of the decision for discontinuation.

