### Statistical methods

#### Major statistical analysis

To examine the treatment effect parameters of all randomly assigned subjects in the primary analysis set, we will analyze the primary outcome according to the intention-to-treat principle. The significance level will be 5% and one-sided. The analysis was based on the analysis of a previous randomized, wait-listed, controlled trial of psychotherapy in cancer patients [48]. First, two-way repeated measures analysis of variance (ANOVA) will be conducted to examine the main effect of the intervention based on intervention status, with timing (pre-intervention, post-intervention, and 4 months post-intervention) and intervention status (intervention group and waiting group) as the independent variables and the primary endpoint, BDI-II score, as the dependent variable. Next, one-way repeated measures ANOVA will be conducted to integrate data from the intervention and waiting groups and to examine changes in BDI-II scores by time (pre-intervention, post-intervention, and 4 months after intervention) in both groups. When there is any missing data, we will employ multiple imputation.

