#### Patient disadvantages and how to minimize them

Since this is a study examining the effects of BA, a behavior-focused psychotherapy, on depression in patients with advanced cancer, we believe that the physical and psychological disadvantages to the study participants will be minimal. However, we will give due consideration to their physical and psychological condition, bearing in mind that they might experience stress due to the content of the intervention program and questionnaires. If exclusion criteria are met during the waiting period, such as worsening of psychiatric symptoms, the patient’s participation will be stopped immediately, and appropriate medical treatment, such as a visit to the psychiatry department of each research facility, will be provided. In addition, patients with a BDI- II score of 21 (moderate) or higher will be enrolled if they wish to participate in the study after being fully informed that they might benefit from pharmacotherapy and the study will be terminated immediately and they will be switched to regular psychiatric care if they experience worsening of psychiatric symptoms based on the discontinuation criteria.

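### Waiting patients who come to need medication are excluded from the study, yet the primary analysis is intention to treat: discontinue their schedule, but still collect the T2 BDI-II

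*Protocol article*

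**What the plan says.** All references are to the protocol article.

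- **Exclusion criteria.** Waiting patients are told that if they come to need medication while waiting, "they will be excluded from the study but can be offered another program equivalent to the BA program if they wish". Temporary emergency use of a psychotropic drug after enrolment is allowed.
- **Patient disadvantages and how to minimize them.** "If exclusion criteria are met during the waiting period, such as worsening of psychiatric symptoms", the patient's "participation will be stopped immediately" and treatment is arranged.
- **Discontinuation criteria.** Criterion 2 is "worsening of physical or psychiatric symptoms, or emergence of new symptoms that make it impossible to continue the intervention". Criterion 5 is "regular use of psychotropic drugs at the discretion of the attending physician during the implementation of the program or while waiting". Both can apply to intervention patients. Criterion 6, meeting an exclusion criterion while waiting, applies only to the waiting arm. At discontinuation the date is recorded and "the reason for discontinuation will be noted on the case registration form".
- **Study procedure.** Assessments are 4 months apart, with none between T1 and T2. A registered patient stays in the database unless consent is withdrawn.
- **Major statistical analysis.** For all randomised patients, "we will analyze the primary outcome according to the intention-to-treat principle". "When there is any missing data, we will employ multiple imputation".

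**The concern.** The conduct rules and the analysis rule do not fit together. The analysis needs a T2 score from every randomised patient. The conduct rules take patients out of the study before T2, and the trigger is a need for medication or psychiatric worsening, which is closely tied to the primary outcome of depression.

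The waiting arm's only untreated period runs from T1 to T2, so the randomised contrast rests on T2. If a worsening patient leaves without a T2 score, the imputation has only that patient's T1 measurements, taken before the worsening. A model fitted to the patients who stayed will probably impute a score that is too low. In the waiting arm this shrinks the apparent benefit. In the intervention arm, where criteria 2 and 5 can remove worsening patients too, it enlarges it.

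Whether a T2 questionnaire is handed out is a matter of conduct. A later analysis plan can vary its assumptions about an uncollected score but cannot recover it.

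**Working it through.** **Step 1: the texts side by side.** The plan gives no figure on this point, so the first check is of wording.

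| Rule | Effect on a patient removed before T2 |
|---|---|
| Exclusion criteria; Patient disadvantages | Out of the study; participation ends |
| Discontinuation criteria | Date and reason recorded; no outcome assessment mentioned |
| Study procedure | Registration kept; follow-up neither promised nor ruled out |
| Major statistical analysis | Patient is in the analysis set; a missing T2 is imputed |

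The patient is therefore analysed, but no rule says the T2 score will exist.

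**Step 2: inputs for the size.**

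- Planned enrolment 38, randomised 1:1: 38/2 = 19 per arm (Power and sample calculation; Fig. 1 caption).
- Minimal important difference 3.5 points, standard deviation 7.84, r = 0.50 (Power and sample calculation). I take r as the correlation between baseline and follow-up.
- Removals per arm are not in the document. I assume k = 0 to 4.
- The error per imputed score, D, is not in the document. I assume imputation is D = 3.5 points too low.

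**Step 3: shift in one arm's mean** = k × D/19.

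| k | k × 3.5/19 |
|---|---|
| 1 | 0.18 |
| 2 | 0.37 |
| 3 | 0.55 |
| 4 | 0.74 |

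**Step 4: net shift in the contrast** (waiting minus intervention) = (intervention removals − waiting removals) × 3.5/19.

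- 3 waiting, 1 intervention: (1 − 3) × 0.184 = −0.37.
- 2 and 2: 0.
- 1 waiting, 3 intervention: (3 − 1) × 0.184 = +0.37.
- Extremes (4 in one arm, 0 in the other): ±0.74, which is 0.74/3.5 = 21% of the target difference.

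**Step 5: comparison with sampling error.** The standard error of the difference is 7.84 × √(2/19) = 2.54. With baseline adjustment it is 2.54 × √(1 − 0.50²) = 2.20. The extreme shift is about 0.3 of a standard error.

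**Step 6: sensitivity to D.** If each imputed score were a full standard deviation too low, four removals in one arm and none in the other would give 4 × 7.84/19 = 1.65 points, or 47% of 3.5. Neither the four removals nor that D has support in the document. It is an outer case.

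**The case against.** **Loss of T2 is inferred.** No sentence says that questionnaires stop at removal. Several discontinuation criteria speak of stopping the intervention, not follow-up. Registration is kept, and the intention-to-treat statement is compatible with continued assessment. The full protocol may provide for it. This stands as a limit on confidence. It does not remove the conflict, because being excluded from the study and having participation stopped are stated rules that a site would reasonably read as the end of follow-up.

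**The size is small and assumed.** This also stands, and it limits how strongly the point can be put.

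A reader might infer four stronger things, which the document does not support:

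- *That the trial is biased against the program.* Criteria 2 and 5 also remove intervention patients, and the balance between arms is unknown.
- *That the equivalent program seriously contaminates the waiting arm.* If T2 were collected after a full program effect, 3.5 points would become 3.5 × (1 − 4/19) = 2.76 with four such patients. But Study procedure and the Fig. 1 caption give the program 4 months, the same as the wait, so a program begun after removal would usually be incomplete at T2. The Interventions section gives a much shorter span, but the 4-month figure is stated twice and sets the assessment interval.
- *That no analysis could address the gap.* With the recorded reason and the T1 scales, a delta-adjusted analysis can show how far conclusions depend on these patients.
- *That a BDI-II at removal is essential.* I simulated removal of the 1 to 4 worst of 19 patients mid-wait, assuming correlations of 0.5 between T1 and T2 and 0.7 between the mid-wait score and each. Imputation from T1 alone put the arm mean about 0.27 to 0.75 too low. Carrying the removal score forward put it about 0.23 to 0.65 too high. That is a similar error with the opposite sign. The planned imputation also could not learn how that score relates to T2, because patients who stay would not have one.

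**Conclusion.** The point holds as a conflict between the stated removal rules and the stated analysis. Taken literally, patients removed for depression-related reasons have no T2 score and are imputed from T1 data.

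The effect on the contrast is probably modest: up to about 0.74 points either way, against a standard error of about 2.5 (2.2 with baseline adjustment). That range rests on two assumptions, 0 to 4 removals of 19 per arm and a 3.5-point error for each, and its sign is unknown. The case for change is that the remedy is cheap and the T2 scores cannot be collected afterwards. It is not that a large bias has been shown. The change should be made, but the point does not by itself undermine the trial. Confidence is medium, because the full protocol might already provide for follow-up.

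**What to change.** 1. Keep the offer of care, including the equivalent program. Replace exclusion from the study and stopping of participation with discontinuation of the assigned schedule, with follow-up continuing.
2. Collect the scheduled T2 and later BDI-II in all discontinued patients in both arms, with their agreement.
3. Record the start dates of medication and of the equivalent program.
4. Analyse observed T2 scores as randomised. Add a delta-adjusted sensitivity analysis for T2 values that are still missing or were obtained after rescue treatment.

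A BDI-II at removal is optional and not needed for this fix.

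The cost is a wording change, already scheduled questionnaires in a few more patients, two dates and one extra analysis. The drawbacks are a small burden on patients who are doing worse, and a main analysis that includes any effect of rescue treatment.

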#### Discontinuation criteria

The discontinuation criteria will be as follows: (1) serious adverse events or adverse reactions that make it difficult to continue the intervention; (2) worsening of physical or psychiatric symptoms, or emergence of new symptoms that make it impossible to continue the intervention; (3) patient desire to discontinue the intervention; (4) interval of 1 month or more between sessions attended; (5) regular use of psychotropic drugs at the discretion of the attending physician during the implementation of the program or while waiting; (6) meeting the exclusion criteria while waiting; and (7) any other reason for which the attending physician deems it necessary to discontinue the intervention.

If this study will be discontinued, the date on which the decision for discontinuation was made and the reason for discontinuation will be noted on the case registration form. The data center will be informed of the discontinuation.

If serious adverse events or adverse reactions, such as worsening of psychiatric or physical symptoms, occurs and it is deemed difficult to continue the intervention, the therapist will promptly inform the research director at each research institution and discontinue this study. The research director at each research institution contacted will promptly inform the research representative and data center of the decision for discontinuation.

### Interventions

The program consists of seven 50-minute sessions conducted over 1–2 weeks, with an average of 5–10 minutes of homework per day. The themes and contents of the program are shown in Table 1. Whenever possible, sessions will be held on the same day as examinations or consultations with the attending physician to improve adherence to intervention protocols.

**Table 1 Tab1:** Themes and contents of the behavioral activation program

Session	Theme	Contents
1	Let’s begin!	• Understand the relationship between emotions and behaviors • Learn tips on how to avoid being preoccupied by cancer in order to regain pleasure and meaning in life
2	Identify the relationship between emotions and behaviors	• Explore the relationship between emotions and daily activities • Identify patterns of anxiety, depression, and calmness
3	Identify activities that make your life pleasurable	• Clarify life values • Identify activities that are achievable in one’s current situation
4	Review the results of activities	• Evaluate the usefulness and difficulty of each activity • Discuss ways to participate in challenging activities
5	Identify difficult situations and understand ways to change one’s feelings	• Identify situations that are likely to lead to anxiety and depression • Identify thoughts that occur in the early stages of anxiety and depression as well as any vicious cycles that might be involved • Identify pros and cons of negative thinking
6	Learn to live a life of value	• Review how the program helped change patterns of daily life • Identify future goals and make plans to achieve them
7	Wrap-up and graduation	• Review what has been learned through the program • Identify future issues and how to address them

This program was verified in a pilot study that explored the applicability of BA to patients with cancer [19]. The pre-post study suggested that the program was feasible and effective for depression in patients with cancer [26].

All therapists will be clinical psychologists or psychiatrists with clinical experience that includes working with patients with cancer and have sufficient experience conducting BA either during the pre-post study [26] or through BA training. A therapist is certified in BA training upon completion of the following three steps: (1) learning about the aims of BA, session structure, and how to proceed by attending an in-person or video training; (2) conducting BA with supervision at least once; and (3) being approved by a supervisor to perform BA.

The individuals responsible for measuring outcomes and assessing patients will differ from those who are responsible for conducting the program. While this program will not impact the patients’ regular treatment in any way, special psychotherapies such as BA (conducted elsewhere) and CBT are prohibited.

### Study procedure

Information about the study will be communicated to each department of each research institution through postings, in-hospital e-mails, websites, and other means. The contact information of the research office will be clearly indicated. Patients who visit each research institution during the study period and wish to participate in the study after recommendation by their attending physician, and those who wish to participate in the study on their own and whose attending physicians determine that their participation is appropriate, will be selected from among those who meet the eligibility criteria and who do not meet the exclusion criteria. For patients who meet the eligibility criteria but not the exclusion criteria, the therapist will provide a detailed explanation during the preliminary interview and obtain their consent to participate in the study. Once consent is obtained, the therapist will confirm the eligibility and exclusion criteria other than the BDI-II score and ask the research assistant to administer questionnaires. The research assistant will ask the participant to fill out the BDI-II questionnaire and transfer the data (entry number, anonymized subject information, and T1 outcome data) to the data center with the entry number written on the case registration form. If the BDI-II score is 16 or higher, the patient will be registered in this study. Once a patient is registered, the registration will not be cancelled (deleted from the database) except in the case of withdrawal of consent, including refusal to use the data for research purposes. In the case of duplicate enrollment, the first enrollment information will be used.

The intervention and each assessment scale will be evaluated using the following process (Figs. 1 and 2). The University Hospital Medical Information Internet Data and Information System for Clinical and Epidemiological Research (UMIN INDICE) allocation software program will be used for case enrollment and randomization of intervention groups in this study. Randomization was stratified by study site with the minimization method to balance the gender (male, female) and the age of the participants at study entry (age 20 ≦ to < 40, age < 65, age 65 to < 100). For allocation concealment to research assistants who administer questionnaires, the allocation will be communicated to the person in charge at each site based on the allocation list prepared by the data center. In addition, the interval between T1 and T2, T2 and T3, T3 and T4 will be 4 months respectively, which is the same length of time it would take if the intervention group had implemented the program, so that research assistants will not be able to identify the allocation group based on the timing of evaluations. The allocation schedule will be kept at the data center until the end of the study. A psychiatrist or psychologist from each institution will be in charge of a total of seven intervention sessions. Outcome measures will be evaluated at three times (T1–T3) in the intervention group and four times (T1–T4) in the waiting group by research assistants who are not involved in the intervention program. Outcome measures will include the BDI-II score as the primary outcome measure and Generalized Anxiety Disorder-7 (GAD-7), Functional Assessment of Cancer Therapy-General (FACT-G), Functional Assessment of Chronic Illness Therapy - Spiritual Well-Being 12 Item Scale (FACIT-Sp-12), Behavioral Activation for Depression Scale-Short Form (BADS-SF), the Valuing Questionnaire (VQ), Numerical rating scale (NRS), and the Integrated Palliative care Outcome Scale (IPOS) scores as secondary outcome measures.

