### Power and sample calculation

Based on the results of a previous study [47], the minimal clinically important difference of the primary endpoint, BDI-II, is 3.5 points. In our pre-post study of patients with cancer and depression [26], the standard deviation was 7.84 points. Many studies have demonstrated the effectiveness of BA in depression with a high level of evidence [23–25]. We hypothesized an alternative hypothesis that intervention group would have lower mean post-intervention scores on the BDI-II than waiting group. The sample size was calculated using a one-tailed test with α = 0.05, power (1-β) = 0.80, and r = 0.50 for the mean value of the two groups. Since 3 (9.4%) out of 32 participants dropped out of the aforementioned pre-post study [26], we assumed that 10% would drop out in this study as well, defined as patients that did not meet the exclusion criteria and discontinued participation. Thus, the total planned enrollment was set to 38 patients.

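### The primary repeated measures ANOVA uses T1 BDI-II only as an outcome level and omits the allocation factors, which gives up precision the trial could have

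*Protocol article*

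**What the plan says.** **Allocation.** Under Study procedure, the protocol article says "Randomization was stratified by study site with the minimization method to balance the gender" and the age of participants, in three bands. The same section makes a T1 BDI-II score of 16 or higher the condition for registration, so every randomised patient has a baseline value.

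**Primary model.** Major statistical analysis specifies a two-way repeated measures ANOVA to examine the main effect of the intervention. Its terms are timing at three levels (before, after, and 4 months after the intervention) and "intervention status (intervention group and waiting group) as the independent variables and the primary endpoint, BDI-II score, as the dependent variable". No covariate is listed there or in the Abstract, which gives the same two factors. The secondary scales use the same two factors.

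**Test level and planning figures.** "The significance level will be 5% and one-sided". Under Power and sample calculation, "The sample size was calculated using a one-tailed test" with power 0.80 and r = 0.50 "for the mean value of the two groups". The article adds that "the minimal clinically important difference of the primary endpoint, BDI-II, is 3.5 points", that in the pre-post study "the standard deviation was 7.84 points", and that "we assumed that 10% would drop out in this study as well". Planned enrolment is 38, randomised 1:1.

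**The concern.** With 38 patients, about 34 of them evaluable, precision is the scarce resource. Two features of the stated model waste some of it.

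First, T1 BDI-II is measured before treatment and is not a minimisation factor. As a level of timing, it is used at best as a change score (through a group-by-time contrast). At worst it is averaged into the group main effect, where a pre-treatment score can carry no treatment effect and only dilutes the contrast. As a covariate, it would remove the part of the outcome variance that it predicts.

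Second, allocation is balanced on site, gender and age, but the analysis does not reflect this. If those factors predict BDI-II, their variance stays in the error term of a between-arm comparison although the design has already balanced it.

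The stake is a lower chance of detecting a real effect, using data that will be collected anyway.

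**Working it through.** **Inputs.** Difference 3.5, SD 7.84, one-sided 5%, r = 0.50, 10% dropout and N = 38, all from the sections named above. Evaluable patients: 38 × 0.9 = 34.2, so 17 per arm. *Assumption:* r is the correlation between any two BDI-II time points. The article's wording does not define it, so r = 0.3 and r = 0.7 are shown as well.

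**The article's own figure.** A paired formula gives SD of difference = 7.84 × √(2(1 − 0.5)) = 7.84. A noncentral-t calculation at 80% power then needs 33 patients. Taken up to an even 34, 34/0.9 = 37.8, i.e. 38. So 38 is reproduced by a paired or within-subject formula. A comparison of two independent arms needs 2 × (1.645 + 0.842)² × (7.84/3.5)² ≈ 62.0, so 63 per arm and 126 in total before dropout. With baseline as covariate, the factor 1 − 0.5² = 0.75 gives about 46.5, so 47 per arm and 94 in total.

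**Power at 17 per arm.** Unadjusted standard error: 7.84 × √(2/17) = 2.69. Base noncentrality: 3.5/2.69 = 1.30. Each analysis changes it as follows:

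- Post-only: variance factor 1, 32 df.
- Change score (the two-time group-by-time contrast): variance factor 2(1 − r), 32 df.
- ANCOVA on T1: variance factor 1 − r², 31 df.
- Three-time group main effect: variance factor (1 + 2r)/3, 32 df. The effect is diluted to 2/3 of 3.5 if present at both later times, or 1/3 if present only at the first.

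| Analysis | r = 0.3 | r = 0.5 | r = 0.7 |
|---|---|---|---|
| Post-only | 0.355 | 0.355 | 0.355 |
| Change score | 0.285 | 0.355 | 0.500 |
| ANCOVA on T1 | 0.378 | 0.431 | 0.555 |
| Main effect, both later times | 0.315 | 0.273 | 0.243 |
| Main effect, first later time only | 0.144 | 0.130 | 0.121 |

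At r = 0.5 the noncentralities are 1.30 (post-only or change), 1.30/√0.75 = 1.50 (ANCOVA), and 1.30 × (2/3)/√(2/3) = 1.06 or half of that, 0.53 (main effect). The difference detectable with 80% power is 6.83 points without baseline as covariate and 5.92 with it.

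**How far this depends on r.** The variance ratio of ANCOVA to change score is (1 − r²)/(2(1 − r)) = (1 + r)/2, which is below 1 for every r below 1. Against post-only it is 1 − r², below 1 for any non-zero r. The size of the gain depends on r; its direction does not.

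**Adding site, sex and age to ANCOVA at r = 0.5.** Site takes 2 df, sex 1 and three age bands 2, so 5 df in all (31 to 26; critical t 1.70 to 1.71). If they explain none of the residual variance, power is 0.428. If they explain 5%, 10% or 20% (an assumed range; the article gives no figure), it is 0.443, 0.459 or 0.497. Continuous age instead of bands saves one degree of freedom.

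**The case against.** **This belongs in the SAP.** The article condenses a full protocol, and covariate lists are often left to the SAP. Nothing says that the model is unadjusted. That is fair as a caution. However, the article does name the independent variables of the primary model, and the Abstract repeats them. A SAP that added covariates would be changing a published model. The point concerns what is stated.

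**Baseline is already in the model.** This is correct. A reader might infer that T1 BDI-II is ignored, but it is the first level of timing, and a group-by-time contrast would subtract it. Correcting for chance baseline imbalance is therefore not unique to ANCOVA. What stands is the loss of efficiency, which is larger for the main effect that the article names.

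**The standard error is not necessarily too large.** A reader might infer that omitting site, gender and age makes it too large as a matter of fact. The document does not support that. It holds only if those factors are prognostic and the contrast is between subjects. In a change score, any effect of theirs that is constant over time cancels within each patient. The article gives no evidence on their prognostic value.

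**r is not defined as a pre-post correlation.** This stands, and is why a range is shown.

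**The remedy alters the primary question.** This also stands. A T2 contrast takes the later time points out of the primary test, so the change has to be declared.

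**Conclusion.** The point holds as a matter of precision. The stated primary model uses T1 BDI-II less efficiently than it could and leaves out the allocation factors. Under the assumption that r = 0.50 is the pre-post correlation, with 17 evaluable per arm, baseline as covariate raises power for 3.5 points from 0.355 to 0.431 against a change-score or post-only contrast. That rise should not be read as the gain over the article's named test. The three-time group main effect stands at 0.273 or 0.130, depending on whether the effect lasts, and moving away from it also changes what is estimated.

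The benefit of site, sex and age is conditional and cannot be sized from the document; their cost is negligible. It would also be wrong to infer that adjustment rescues the sample size. Power stays near 0.43 against the planned 0.80, because 38 matches a paired-type calculation and not a comparison of two arms. That is a separate and larger problem.

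**What to change.** Specify the primary analysis as the between-arm difference in BDI-II at T2 (4 months), the last assessment before the waiting group starts the programme. Estimate it by ANCOVA, or as the T2 contrast of a mixed model, with T1 BDI-II as covariate plus site, sex and continuous age. Continuous age avoids sparse bands. Analyse each secondary scale in the same way with its own T1 value, and report the unadjusted difference as a sensitivity analysis.

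State openly that this replaces the three-time main effect as the primary test, and report later time points separately. Define r in the sample size section.

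The cost is an amended analysis paragraph, about 4 to 5 model degrees of freedom for the allocation factors, and a declared change of primary test, best made before any outcome data are examined. No new data are needed.
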